**Figure 1 F1:**
[figure not shown]
Participant enrolment flow chart. ED, emergency department.

Enrolled participants will have their medical records reviewed, and relevant de-identified data will be extracted and entered directly into a password-protected Research Electronic Data Capture (REDCap) electronic database. Data to be extracted are outlined in box 2. Age was measured in months for children <2 years of age and in years for children ≥2 years of age. Indigenous status was defined using local ethnicity criteria, where applicable (eg, Aboriginal or Torres Strait Islander in Australia; Māori or Pasifika in New Zealand). Comorbidities were defined using the Pediatric Complex Chronic Condition system.^21^ We included primary site of infection and primary pathogen causing sepsis in the data collected. We did not collect inflammatory markers such as C-reactive protein or procalcitonin.

Box 2Data to be collected by all participating EDs by time pointInitial ED attendanceDetailed patient demographic information (age, sex, Indigenous status, comorbidities)Vital signs (^β^HR, MBP, SBP, RR, SpO2, GCS score, CRT)Pathology tests (^χ^VBG, FBC, UEC, LFT, coagulation profile, troponin)Therapies administered (antibiotics, oxygen, fluids—bolus/maintenance/drug administration line, steroids, organ support)Admission diagnosisDuring hospital stayDisposition (hospital ward, ICU)Vital signs (6, 12, 18 and 24 hours from ED arrival)Pathology tests (6, 12, 18 and 24 hours from ED arrival)Therapies administered (duration of hospitalisation censored at 30 days)ICU and hospital length of stay (censored at 30 days)Discharge diagnosisResults of all microbiological testsIn-hospital mortality (censored at 30 days)CRT, capillary refill time; ED, emergency department; FBC, full blood count; ICU, intensive care unit; LFT, liver function test; MBP, mean blood pressure; RR, respiratory rate; SBP, systolic blood pressure; UEC, urea electrolytes creatinine; ^α^GCS, Glasgow Coma Scale; ^β^HR, heart rate; ^χ^VBG, venous blood gas.

All research team members across participating sites will receive formal training by the central coordinating team, covering study processes and the completion of the REDCap database electronic clinical report form prior to commencing enrolment. Standardised teaching materials and procedures have been developed and will be distributed to all participating sites. A source data plan will be established at each site to ensure consistency in data. The central coordinating team will conduct monthly data audits, and any data queries will be communicated to the respective sites for resolution.

### Data management

Data collected from the medical records will be entered into a password-protected database enabled through the REDCap web-based application hosted by the Murdoch Children’s Research Institute (MCRI).^22^ This database will only be accessible to trained research staff. All data entered into this database will be de-identified. All sites will maintain a separate password-protected logbook on a local secure online database containing identifying information for data queries. Each site will have access to their individual site data only. Oversight of recruitment, study processes and compliance with data collection and data entry procedures will be conducted remotely, as detailed in the study manual of operations. If there is a need to re-identify data for clarification, this will be done by the principal investigator (PI) at the site level. All local data will be retained in line with the ethics and governance requirements of the local site. The Trial Steering Committee consisting of the Chief PI, trial coordinator and trial statistician will meet quarterly to discuss the progress of the study and review recruitment and data management.

## Statistical methods

### Sample size and power calculation

We aim to enrol more than 5000 children over 12 months. This will provide a large sample for describing the international sepsis landscape. No formal sample size calculation was undertaken due to lack of prior data regarding sepsis incidence. Where applicable, appropriate power calculations will be included in future papers describing specific outcomes using the database.

Descriptive statistics will be calculated for key epidemiological variables, using means and SD for normally distributed data, and medians and IQRs for skewed data. We will apply existing organ dysfunction criteria following the STARD and clinical decision rule guidelines.^15 23^ Organ dysfunction criteria will be based on the organs and cut-off points used in paediatric Sequential Organ Failure Assessment, Pediatric Logistic Organ Dysfunction-2(PELOD-2), quick Sequential Organ Failure Assessment, quick Paediatric Logistic Organ Dysfunction-2 and the Phoenix sepsis criteria.^24^ Completely missing values will be considered non-additive to organ dysfunction scores in keeping with their original validation studies.^11 25^ The level of significance will be set at p<0.05.

The feasibility of inclusion criteria and outcomes for use in the design and conduct of future international interventional trials will be assessed using prevalence, severity, outcome and treatment data from this study.

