Many challenges contribute to the lack of accurate reporting of sepsis epidemiology, severity and therapies in children, with the major contributor being inconsistency in the methods used for case ascertainment. International Classification of Disease codes have been used to retrospectively identify children with sepsis or infection-related organ dysfunction, with a sevenfold difference in incidence found between these two case ascertainment methods.^9^ Case ascertainment using International Sepsis Consensus Conference criteria has been found to be discordant with clinician ascertainment of sepsis, with an inter-rater agreement (kappa) of 0.57.^10^ Recently, the Society of Critical Care Medicine has derived and validated the international consensus-based Phoenix criteria to diagnose and report sepsis in children, based on measures of dysfunction of four organs after the initial 24 hours of hospitalisation.^11^ There remain questions, however, regarding the applicability of these criteria in the emergency department (ED) and early in hospitalisation, the impact of missing organ dysfunction data (particularly in low- and middle-income countries (LMICs)) and the test characteristics of the Phoenix sepsis criteria for predicting mortality.^12 13^ Ideally, data used as diagnostic criteria from across countries are collected in a way that allows comparison between populations.

In an international collaboration between emergency physicians, paediatricians and intensivists, this study will develop the first database for children with community-acquired childhood sepsis in LMIC and select HIC. We will describe sepsis prevalence, severity and outcomes. We will report current management practice and antimicrobial use. We will apply diagnostic criteria and risk stratification criteria to allow standardised comparisons across diverse populations. This study will provide the critical understanding of the epidemiology of children with suspected sepsis as a basis for future interventional trials.

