## Discussion

This is the first international database that will allow a comprehensive description of sepsis epidemiology. This will improve the understanding of global sepsis incidence, severity and outcomes, and allow for comparison between diverse populations. Prior global epidemiological studies have focused on the point prevalence of sepsis in critical care populations or global estimates of disease burden.^5 27^ Building on these prior efforts, we will explore differences in aetiology of sepsis and allow comparisons of management of sepsis including patterns of antimicrobial use between populations. Standardised criteria for sepsis diagnosis and risk stratification will be applied to the study cohort, providing a benchmark for between-population comparison. Finally, this study will provide baseline data and feasibility data for the conduct of future interventional trials.

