This study has several limitations. Standard practice will be decided by the treating clinician, with inherent differences in thresholds for diagnosing and treating sepsis and therapies administered. Where no test for organ dysfunction was obtained at baseline in the ED, the result will be assumed to be normal, although this may not be the case. While multiple EDs are included in this study, most are tertiary referral centres and may not reflect the population seen in rural, community and regional centres. The study focuses on community-acquired sepsis, while hospital-acquired sepsis is a significant contributor to sepsis morbidity and mortality. Though we include participants <18 years, study sites may have different age thresholds for treating older adolescents, which may skew study age demographics. The study inclusion criteria differ from those used in the derivation and validation of the Phoenix sepsis criteria, which retrospectively collected data from the pre-COVID-19 era.^11^ We did not use microbiological testing as an inclusion criterion because many hospitals post COVID-19 performed routine microbiological testing in children in whom sepsis was not suspected. Nevertheless, our inclusion criteria when applied to two HICs identified remarkably similar cohort of patients to the Phoenix derivation and validation cohort.^12^ We did not collect data on inflammatory markers such as C-reactive protein or procalcitonin as they are not included in any sepsis diagnostic criteria or risk stratification criteria. We did not collect data including the Pediatric Index of Mortality-3 or Pediatric Risk of Mortality-3 as these scores were developed for use in the ICU setting.^28 29^ We did not collect any socioeconomic status measurements, limiting the ability to understand the impact of health inequality on outcomes.

This study will provide a unique landscape analysis across LMICs and HICs using standard data collection and measures of sepsis severity. It has the potential to influence future clinical practice, antimicrobial stewardship, public policy and sepsis research conduct in major urban centres globally.

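### Scoring missing organ-dysfunction tests as zero can turn a gap in test availability between LMIC and HIC sites into an apparent gap in severity or score accuracy, and the time window of the rule is unclear

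*Protocol article*

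**What the plan says.** All references are to the protocol article.

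- **Rule in the methods** (Statistical methods, under Sample size and power calculation): "Completely missing values will be considered non-additive to organ dysfunction scores in keeping with their original validation studies".
- **Rule in the limitations** (Discussion): "Where no test for organ dysfunction was obtained at baseline in the ED, the result will be assumed to be normal". The same sentence concedes that this may be untrue.
- **Expected pattern of missingness** (Introduction): among the open questions about the Phoenix criteria is "the impact of missing organ dysfunction data (particularly in low- and middle-income countries (LMICs". No rate is given.
- **Use of the scores** (Discussion): "Standardised criteria for sepsis diagnosis and risk stratification will be applied to the study cohort, providing a benchmark for between-population comparison". The statistical section adds: "We will apply existing organ dysfunction criteria following the STARD and clinical decision rule guidelines". The Design section also invokes STARD for validating the criteria.
- **Data available**: Box 2 collects tests at the initial ED attendance and then "Pathology tests (6, 12, 18 and 24 hours from ED arrival" onwards through the first day.
- **Setting**: 25 of 34 sites are in LMICs and 9 in HICs (Setting and participants). Data come from retrospective record review, and the Discussion leaves standard practice to the treating clinician, so the study mandates no test.

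**The concern.** A zero for an untested component makes the score reflect both the child's condition and whether the test was done. Within one hospital with stable practice this may be tolerable. Across settings it matters, because the article itself expects missingness to be a particular issue in LMICs and then uses the scores to compare populations.

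With the same disease, a setting that tests fewer of its abnormal children would show less organ dysfunction, lower scores and lower sensitivity for death. That could be reported as a true population difference, or as poor performance of the criteria in LMICs. Both conclusions would feed into the inclusion criteria and outcomes of the interventional trials that this study is meant to inform.

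The two statements of the rule also differ in scope. One concerns values that are *completely missing* and gives no window. The other concerns tests not done at ED baseline. A child with no ED blood test and an abnormal 6-hour result falls between them.

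**Working it through.** The plan gives no calculated figure on this point, so there is none to reproduce. Everything below is illustration.

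**Inputs from the article:** 25 LMIC and 9 HIC sites; target above 5000 children; significance level 0.05.

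**Inputs assumed:** true dysfunction on one component p = 20% in both settings; HIC availability 95%; LMIC availability 90% down to 40%; equal enrolment per site; two-sided test; clustering by site ignored.

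**1. Observed prevalence.** With untested scored as normal, observed prevalence = p × a, where a is the probability that a truly abnormal child is tested. HIC: 0.20 × 0.95 = 19.0%.

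| LMIC availability | Observed LMIC | Ratio to HIC | Chance of p<0.05 with no true difference |
|---|---|---|---|
| 90% | 18.0% | 0.95 | 13% |
| 80% | 16.0% | 0.84 | 70% |
| 60% | 12.0% | 0.63 | >99% |
| 40% | 8.0% | 0.42 | >99% |

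The last column uses 5000 × 25/34 = 3676 LMIC and 1324 HIC children. For the 80% row, the pooled rate is (3676 × 0.16 + 1324 × 0.19)/5000 = 0.168. The standard error is 0.0120 under no difference and 0.0124 under the observed rates. The chance is then Φ[(0.03 − 1.96 × 0.0120)/0.0124], about 70%. With p = 10% or 40% in place of 20%, it is 40% or 98%.

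**2. Accuracy.** If testing is independent of status and outcome, observed sensitivity = a × Se and observed specificity = 1 − a × (1 − Sp). Taking Se = Sp = 0.80:

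- a = 80%: sensitivity 0.64, specificity 0.84
- a = 60%: sensitivity 0.48, specificity 0.88
- a = 40%: sensitivity 0.32, specificity 0.92

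Sensitivity falls and specificity rises. The single-cut-off AUC, (Se + Sp)/2, falls from 0.80 to 0.74, 0.68 and 0.62.

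**3. Counter-case: targeted testing.** Suppose 95% to 100% of abnormal children are tested but only 40% of the others. Zero-scoring gives 0.20 × 0.95 = 19% to 0.20 × 1.00 = 20%, close to the truth. Restricting to tested children gives 0.19/(0.19 + 0.80 × 0.40) = 37% to 0.20/(0.20 + 0.32) = 38%, which is far worse.

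**4. What a bounding analysis would show.** With missing set to abnormal and testing independent of status, the upper bound is p × a + (1 − a). For HIC at 95% this is 0.19 + 0.05 = 24%. For LMIC at 80% it is 0.16 + 0.20 = 36%. The ranges, 19% to 24% and 16% to 36%, overlap, so the observed 3-point gap would not by itself show a difference in disease.

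**5. Time window.** Suppose 70% of abnormal children are tested at baseline, 20% first at 6 to 24 hours and 10% never. A baseline-only rule gives 0.20 × 0.70 = 14%. A rule counting any test within 24 hours gives 0.20 × 0.90 = 18%. The two readings differ by 4 points against a true 20%.

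**The case against.** The case for leaving the text alone has weight.

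- **Zero-scoring is presented as the scores' own convention.** The article ties it to the validation studies. Those are not at hand, so this cannot be checked, but comparability with them is a sound reason to keep the rule as the reference. It does not make LMIC and HIC scores comparable with each other.
- **The assumption is disclosed.** The Discussion lists it as a limitation. What it does not say is that the error may differ by setting, which is what would damage a benchmark.
- **Sensitivity analyses often sit in an SAP.** None is shown here, so their absence from the article is not a fault. The point rests on the rule that is stated and the use to which the scores are put.
- **The main aim is the database.** The analysis is largely descriptive, no LMIC-versus-HIC test is specified, and the raw data will still show what was measured. Nothing irreversible is fixed.

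A reader might infer more than the documents support:

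- *That the LMIC/HIC comparisons are biased.* No availability rate is given. Bias requires availability among truly abnormal children to differ, and under targeted testing it can be close to nil.
- *That every unmeasured test is scored as normal.* Each statement is limited, one to values completely missing and the other to ED baseline.
- *That the two statements contradict each other.* Both give an untested item zero, and they can be read as describing a baseline score and a score over a longer window. Neither says so, and the Discussion does not say that later results are ignored. This is an ambiguity of scope.

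**Conclusion.** The concern stands as a conditional one. Applied alone, the stated rule can convert a difference in test availability into an apparent difference in prevalence, severity or sensitivity, and the article itself supplies the reason to expect such a difference.

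The size is unknown. Under the assumed 20% true dysfunction and 95% versus 80% availability, the artefact is 19% versus 16%. At about 5000 children, with clustering ignored, a gap of that size would often reach p<0.05. With equal availability, or near-complete testing of abnormal children in both settings, it is about zero. These figures concern one component; the effect on a total score depends on how many components are affected.

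Separately, the methods and Discussion statements leave open whether a first abnormal result at 6 to 24 hours counts, and they need to be aligned.

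**What to change.** 1. Keep zero-scoring as the reference analysis, for comparability with the original validation studies.
2. Report the percent measured for each component by site, income group and time point.
3. For LMIC/HIC comparisons and for accuracy estimates, add an analysis restricted to bedside components and a bounding analysis with missing set to abnormal. Imputation is optional, and only where a site measures the component often enough to support it.
4. Interpret between-setting differences in the light of these results, and add to the limitations that the error from assuming normality may differ by setting.
5. Define *completely missing* and its time window once for the baseline score and once for the 24-hour score, and use the same definitions in the statistical section and the Discussion.

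Cost: some wording and modest extra analysis, with no new data. The price is less definite LMIC estimates; the bounds will be wide where testing is sparse.

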### Ethical issues, consent and dissemination

Approval for the conduct of this study was provided by the Royal Children’s Hospital Human Research Ethics Committee (HREC 100648) and is prospectively registered through the Australian and New Zealand Clinical Trials Registry (trial ID: ACTRN12624000052538). The MCRI serves as the primary sponsor for this trial. As this study is an international study, each participating site will be required to obtain local Institutional Research Ethics Board (IREB) approval. Each jurisdiction was consulted to determine the level of consent required. Given the observational non-interventional nature of this study, to date, no sites with IREB approval have been required to obtain consent. The study protocol will follow successful processes used for other large multicentre observational studies performed by the Paediatric Research in Emergency Departments International Collaborative network.^26^

### Risk management, adverse events and patient safety

As an observational study, there are no anticipated adverse events related to the research, except a minor risk of loss of confidentiality.

### Time plan

The study will collect data over a 1-year period (calendar year 2025) at all sites.

## Discussion

This is the first international database that will allow a comprehensive description of sepsis epidemiology. This will improve the understanding of global sepsis incidence, severity and outcomes, and allow for comparison between diverse populations. Prior global epidemiological studies have focused on the point prevalence of sepsis in critical care populations or global estimates of disease burden.^5 27^ Building on these prior efforts, we will explore differences in aetiology of sepsis and allow comparisons of management of sepsis including patterns of antimicrobial use between populations. Standardised criteria for sepsis diagnosis and risk stratification will be applied to the study cohort, providing a benchmark for between-population comparison. Finally, this study will provide baseline data and feasibility data for the conduct of future interventional trials.

This study has several limitations. Standard practice will be decided by the treating clinician, with inherent differences in thresholds for diagnosing and treating sepsis and therapies administered. Where no test for organ dysfunction was obtained at baseline in the ED, the result will be assumed to be normal, although this may not be the case. While multiple EDs are included in this study, most are tertiary referral centres and may not reflect the population seen in rural, community and regional centres. The study focuses on community-acquired sepsis, while hospital-acquired sepsis is a significant contributor to sepsis morbidity and mortality. Though we include participants <18 years, study sites may have different age thresholds for treating older adolescents, which may skew study age demographics. The study inclusion criteria differ from those used in the derivation and validation of the Phoenix sepsis criteria, which retrospectively collected data from the pre-COVID-19 era.^11^ We did not use microbiological testing as an inclusion criterion because many hospitals post COVID-19 performed routine microbiological testing in children in whom sepsis was not suspected. Nevertheless, our inclusion criteria when applied to two HICs identified remarkably similar cohort of patients to the Phoenix derivation and validation cohort.^12^ We did not collect data on inflammatory markers such as C-reactive protein or procalcitonin as they are not included in any sepsis diagnostic criteria or risk stratification criteria. We did not collect data including the Pediatric Index of Mortality-3 or Pediatric Risk of Mortality-3 as these scores were developed for use in the ICU setting.^28 29^ We did not collect any socioeconomic status measurements, limiting the ability to understand the impact of health inequality on outcomes.

This study will provide a unique landscape analysis across LMICs and HICs using standard data collection and measures of sepsis severity. It has the potential to influence future clinical practice, antimicrobial stewardship, public policy and sepsis research conduct in major urban centres globally.
